[figure not shown]

#### DISCLAIMER

*This report was written by the statistical consulting service of the University of Zurich, Epidemiology, Biostatistics and Prevention Institute, Biostatistics Department (IEBP) in collaboration with the Institute for Complementary and Integrative Medicine (IKI). The authors agree that they follow the ICMJE guidelines for authorship, <http://www.icmje.org>.*

**Abbreviations**

|        |                                                         |
|--------|---------------------------------------------------------|
| ANCOVA | Analysis of covariance                                  |
| CTC    | Clinical trial center, University Hospital Zurich (USZ) |
| DRKS   | Deutsches Register klinischer Studien                   |
| EAT    | Expectation of acupuncture treatment                    |
| FPFV   | First patient first visit                               |
| INLA   | Integrated nested Laplace approximations                |
| IQR    | Interquartile range                                     |
| LPLV   | Last patient last visit                                 |
| MAR    | Missing at random                                       |
| MCAR   | Missing completely at random                            |
| MCMC   | Markov Chain Monte Carlo                                |
| MICE   | Multivariate imputation by chained equations            |
| NA     | Not applicable                                          |
| NRS    | Numeric rating scale                                    |
| OS     | Operating system                                        |
| PMM    | Predictive mean matching                                |
| SAP    | Statistical analysis plan                               |
| SD     | Standard deviation                                      |

## 0 Preface

This statistical analysis plan has been written following Gamble et al. (2017).

## 1 Administrative Information

### 1.1 Title and Registration

Statistical analysis plan (SAP) for the trial *Changing Patients' Expectations to Increase Treatment Effects: A Randomized Controlled Study in Chronic Low Back Pain Patients Receiving Acupuncture*. Short Title: *Pain Acupuncture Treatment Expectation (PATE)*.

Trial registration: DRKS00010191 (Deutsches Register klinischer Studien, [www.drks.de](http://www.drks.de)), registration date 30 March 2016.

### 1.2 SAP Version

Version 1.0, May 29, 2018.

### 1.3 Protocol Version

This document is based on Study Protocol Version 2, dated 9 February 2016.

### 1.4 SAP Revision History

| Prev. Version | Updated Version | Sections Changed | Description and Reason for Change | Date of Change |
|---------------|-----------------|------------------|-----------------------------------|----------------|
|               | 0.0             |                  | Creation of document              | 14.02.2018     |
| 0.0           | 1.0             |                  | First final version               | 29.05.2018     |

## 2 Introduction

### 2.1 Background and Rationale

See Study Protocol, Section 3, Introduction, pp. 19–22.

## 2.2 Objectives

This study wants to manipulate pre-treatment expectations in patients receiving acupuncture, and to determine whether expectation can mediate treatment outcomes. The impact of two verbal briefing interventions (one on effectiveness and one on side effects) upon patients' treatment expectation before acupuncture treatment, the experience of side effects during treatment, and pain reduction after treatment will be analysed.

## 3 Study Methods

### 3.1 Trial Design

The trial is a randomized, double-blind (patients and statisticians), four-armed trial with a  $2 \times 2$  factorial design. The factors are effectiveness briefing (regular *vs.* high) and side effects briefing (regular *vs.* intense). The statistical analysis will be conducted blind for allocation of patients.

### 3.2 Randomization

Block-randomization with randomly varying block sizes (either 4 or 8) in a 1:1:1:1 ratio was used. An additional block will be used at the beginning that is not balanced, this means that the final totals in each group may not be exactly equal (but still similar). This made it more difficult to anticipate future assignments as the numbers will not return to equality at the end of each block (Schulz and Grimes, 2002). The randomization sequence was stratified by gender using R (version 3.1.0). For allocation of patients via the internet, the software secuTrial® (Clinical Trial Center, University Hospital Zurich) was used.

### 3.3 Sample Size

For sample size calculation, nQuery Advisor (version 7.0) was used.

#### 3.3.1 Research Question 1a

No previous data on expectancy change were available for trial planning purposes. For this study, the assumption was that the high expectation briefing is clinically meaningful better than a regular expectancy briefing in changing expectation, with a standardized mean difference (SMD) of 0.5. Assuming a power of 80% and a two-sided alpha level of 5%, a sample size of 128 patients (64 high expectation briefing and 64 regular expectation briefing) would enable the detection of a difference of SMD 0.5 for the expectancy briefing intervention. Assuming a dropout rate of approximately 15%, 150 patients were sought to be enrolled.

#### 3.3.2 Research Question 1b

With the above mentioned sample size the power is 56–65% ( $n = 128$ –150) to detect a significant difference between high and regular expectation briefing on pain intensity after the acupuncture treatment. This assumption is based on a previous study (Linde et al., 2007) with response rates of 54% in the high expectation group and 39% in the low expectation group that resulted in a SMD of 0.38.

### 3.3.3 Research Question 2

Variation of the outcomes was not known prior to the study. Thus, the sample size was determined using two-group Fisher's exact tests of equal proportions (for binary outcomes). 50% of the patients in the intense safety briefing group and 10% in the regular group were expected to have side effects such that a side effects score can be calculated (Witt et al., 2009). It showed that with 64 patients in each study group such differences in outcome scores could be detected with at least 99% power at a 0.05 two-sided significance level. This power analysis was conservative and the actual power of the study will be higher since a count score and not a binary variable is used.

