## 3.4 Framework and Hypotheses

In a first step, research question 1a will be tested. Only if the high expectation briefing significantly changes the expectations (rejection of null hypothesis 1a), research question 1b concerning the effect on pain intensity will be tested. In both tests, the same significance level of  $\alpha = 0.05$  will be used (see also Section 4.1). This hierarchical order ensures to control for multiple testing.

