## 4 Statistical Principles

### 4.1 Confidence Intervals and $p$ -Values

All confidence intervals are 95% and two-sided. All tests are two-sided and performed at a significance level of 0.05.

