### 6.2.2 Research Question 1b: Average Pain Intensity at the End of Treatment

If the result of the analysis of research question 1a indicates a significant effect of briefing on the expectations of acupuncture treatment, research question 1b will be analysed. The pain intensity will be analyzed using ANCOVA. Outcome variable is the pain intensity (`nrs_8_1`) measured at the end of the acupuncture treatment. Covariate of interest is the effectiveness briefing group (`EXPBRIEF`). As adjustment variables, pain intensity at first visit (`screening_1a_4a`), gender (`pers_1_2`), acupuncture therapist (`acupuncturist`), and baseline optimism (`LOT_BL_optim`) and pessimism (`LOT_BL_pessim`) will be used.

Missing values will be imputed (see Section 6.5). As a sensitivity analysis, the same model will be fitted again, using only complete cases (see Section 6.4). The estimated mean difference of the two briefing groups with 95% confidence interval and  $p$ -value will be reported. The estimated effects of the adjusting variables will not be shown. In addition, adjusted means with 95% confidence intervals will be reported for each treatment group, where all continuous adjustment variables will be fixed at their mean, and the effects of acupuncture therapist and gender will be given equal weights over the factor levels (thus 0.5 for gender and 0.33 for acupuncturist).

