For chronic pain there is a broad consensus about the importance of patient expectations on treatment outcomes (Bialosky et al., 2010; Bishop et al., 2014; Iles et al., 2009). Patient expectations are also important for CLBP and acupuncture as shown in secondary analyses of acupuncture trials. However, those analyses do not allow causal conclusions about the importance of expectations on the pathway along the treatment. Experimental study designs with healthy subjects were successful in changing patient expectations and allow causal conclusions. Pain was successfully reduced by verbal suggestions in experimental studies that altered expectations. Therefore, we want to move the field forward with a study that allows applying an experimental methodology in a clinical setting. This goes along with the suggested implication for research of Bialosky and colleagues: "Further longitudinal studies specific to the experimental manipulation of expectation are needed in clinical samples [...]" (Bialosky et al., 2010). We aim to bridge the gap between experimental placebo research and clinical pain research by using verbal suggestions about the possible effects of acupuncture treatment as an intervention to change patients' expectations and influence treatment outcome (i.e. pain). This will also address the research question if expectations mediate pain reduction. In a second research question, our project will study the nocebo response (i.e. reported side effects) in patients receiving intense and detailed information about the possible side effects of acupuncture.

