### 11.2 Determination of Sample Size

For sample size calculation we used nQuery Advisor (version 7.0).

Research question 1a: No previous data on expectancy change were available for trial planning purposes. For this study, we assume that the high expectation briefing is clinically meaningful better than a regular expectancy briefing in changing expectation, with a standardized mean difference (SMD) 0.5.

Assuming a power of 80% and a two-sided alpha level of 5%, we calculated that a sample of 128 patients (64 high expectation briefing and 64 regular expectation briefing) would enable detection of a difference of SMD 0.5 for the expectancy briefing intervention. Assuming a dropout rate of approximately 15%, we sought to enroll 150 patients.

Research question 1b: With the above mentioned sample we will have a power of 56-65% (n=128-150) to detect a significant difference between high and regular expectation briefing on average pain severity after 4 weeks. This assumption is based on our previous study

(Linde et al., 2007) with response rates of 54% in the high expectation group and 39% in the low expectation group that resulted in an SMD of .38.

Research question 2: Variation of the outcomes was not known prior to the study. Thus, the sample size was determined using two-group Fisher's exact tests of equal proportions (for binary outcomes). We expected to have 50% of patients with side effects to calculate a side effect score in the safety briefing group and 10% in the group without intense safety briefing (Witt et al., 2009). It showed that with 64 patients in each study group such differences in outcome scores could be detected with at least 99% power at a .05 two-sided significance level. This power analysis was conservative and the actual power of the study will be higher since we will use a continuous score and not only a binary variable.

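### The 56–65% power for pain is stand-alone power without the 1a gate, and SAP 6.2.2 makes the primary pain analysis itself, not only its confirmatory test, depend on 1a

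*Combined protocol and SAP*

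**What the plan says.** SAP 3.3.2 gives "With the above mentioned sample size the power is 56–65"% for 1b at n = 128–150. Protocol 11.2 has the same figure: "we will have a power of 56-65% (n=128-150"). Both base it on an earlier study with "response rates of 54% in the high expectation group and 39% in the low expectation group", "that resulted in a SMD of 0.38".

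SAP 3.3.1 sizes 1a for SMD 0.5 with 80% power at 128 patients, and reaches 150 by allowing about 15% drop-out.

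SAP 3.4 sets the order of testing: "Only if the high expectation briefing significantly changes the expectations" is 1b tested, with the same alpha at both steps. Protocol 11.1 and 11.3.2 say the same. SAP 6.2.2 is worded more strongly. It opens with a condition, a significant effect of briefing "on the expectations of acupuncture treatment, research question 1b will be analysed".

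Protocol 3.3 describes the source of the 0.38 as a pooled analysis in which patients' own expectations predicted response. Of secondary analyses of acupuncture trials, protocol 3.1 says that "those analyses do not allow causal conclusions about the importance of expectations".

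**The concern.** The printed power answers a question the plan does not ask: how often a single test of pain, run on its own, would be significant. Under the plan a confirmatory pain result needs two rejections in sequence, and no section gives the power of that procedure. A reader who sets a null pain result against 56–65% may credit the trial with more power for that claim than its stated assumptions imply.

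The effect size adds uncertainty. It contrasts patients who happened to hold high or low expectations, yet it is used undiscounted for a randomised briefing, and the sample-size sections do not repeat the protocol's own caveat.

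The condition in SAP 6.2.2 is a separate matter. A fixed testing sequence requires only that the confirmatory claim be withheld when the first step fails. As worded, the primary estimate of the briefing effect on pain and its confidence interval are not called for either.

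**Working it through.** **Inputs.** Two-sided alpha 0.05 (SAP 4.1: "All tests are two-sided and performed at a significance level of 0.05"). SMD 0.5 for 1a and about 15% drop-out (SAP 3.3.1). SMD 0.38 for 1b (SAP 3.3.2). Allocation 1:1:1:1 in a 2×2 design (SAP 3.2), so 64 or 75 patients per effectiveness-briefing level at n = 128 or 150.

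**1. The effect size.** Probit conversion of the two response rates: z(0.54) − z(0.39) = 0.100 + 0.279 = 0.380. The SMD reproduces.

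**2. The plan's own power.** Noncentral t with df = 2n − 2 and noncentrality d·√(n/2), where n is the number per level.

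| | 64 per level | 75 per level |
|---|---|---|
| 1a, d = 0.5: noncentrality | 2.83 | 3.06 |
| 1a power | 80.1% | 86.0% |
| 1b, d = 0.38: noncentrality | 2.15 | 2.33 |
| 1b stand-alone power | 56.9% | 63.8% |

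The printed 80% and 56–65% both reproduce, the latter to within about one percentage point. The 1b figure is therefore unadjusted and ungated.

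**3. Drop-out.** 150 × 0.85 = 127.5, so the n = 128 end of the range is the number left after the planned drop-out. The n = 150 end assumes none.

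**4. Two-step power.** If the two statistics are independent, this is power(1a) × power(1b). The column for correlation 0.5 (assumed) takes the bivariate normal probability with the marginal powers of step 2. The last column is the logical minimum and maximum: max(0, p1 + p2 − 1) and min(p1, p2).

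| Patients for 1a / pain | Independent | Correlation 0.5 | Bounds |
|---|---|---|---|
| 128 / 128 | 0.801 × 0.569 = 45.6% | 51% | 37.0–56.9% |
| 150 / 128 | 0.860 × 0.569 = 48.9% | 53% | 42.9–56.9% |
| 150 / 150 | 0.860 × 0.638 = 54.9% | 59% | 49.8–63.8% |

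The middle row matters because the 1a questionnaire is completed straight after the briefing and before the first acupuncture session (protocol 9.3.2). Drop-out during treatment should hardly affect it.

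**5. Covariate adjustment.** ANCOVA divides the residual SD by √(1 − r²)⁻¹, so the effective SMD becomes d/√(1 − r²). With an assumed r = 0.4 for both outcomes, 0.5 becomes 0.546 and 0.38 becomes 0.415. Two-step power under independence is then 0.865 × 0.643 = 56% at n = 128 and 0.913 × 0.713 = 65% at n = 150. With r = 0.3 it is 51% and 60%; with r = 0.5, 62% and 72%. The documents give no value for r.

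**6. How often the gate closes.** If the 1a effect is truly 0.5: 1 − 0.801 = 20% at n = 128 and 1 − 0.860 = 14% at n = 150.

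**7. What the SAP makes conditional.** Only SAP 6.2.2, the primary end-of-treatment ANCOVA, expressly depends on 1a. Week-2 pain (6.6.2), the 2×2 model of 1b (6.6.4), follow-up pain (6.6.5), and the bothersomeness and PROMIS pain models in Appendix A carry no stated condition.

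**The case against.** The best defence is that the printed figure is arithmetically correct and openly below 80%, so nobody is told that pain is well powered. That stands: this is a labelling gap, not a calculation error.

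A second defence is that a gated, unadjusted figure is one-sided, because the plan adjusts both analyses for baseline values. At an assumed covariate–outcome correlation of 0.4, two-step power returns to about 56% and 65%. This also stands, and it is why a bare 46% should not simply replace the printed range. It does not rescue the existing text, which neither claims nor quantifies any gain from adjustment and reproduces without one.

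Third, the SAP is dated May 2018, after the last patient visit in December 2017, so restating planning power alters no patient number or test. True, but the condition in SAP 6.2.2 still decides what is reported.

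Three stronger readings are tempting and are not supported:

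- A reader might infer that the power ignores drop-out. It does not, since 128 is the post-drop-out number.
- A reader might infer that pain goes wholly unanalysed if 1a fails. The ungated models listed in step 7 rule that out, and the factorial model includes the effectiveness briefing.
- A reader might argue that the pain effect can only pass through the 0.5 SD shift in expectation, assume slopes of 0.2–0.4, and reach SMDs of 0.10–0.20 with 9–23% power. No section gives such slopes. Full mediation is a hypothesis to be tested (protocol 11.3.2), and the groups also differ in booster visit, letters and written tasks (protocol 8.1, 8.2).

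**Conclusion.** The point holds in a limited form. The 56–65% is stand-alone, unadjusted power. For the two-step procedure actually planned, the plan's own SMDs give about 46%, 49% or 55% under independence, depending on how many patients contribute to each outcome, and about 51%, 53% or 59% at an assumed correlation of 0.5. Without adjustment the ceiling is the stand-alone 57% at 128 with pain data or 64% at 150. Adjustment could offset the loss, to an extent the documents do not allow one to fix.

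The SMD of 0.38 is an assumption carried over from a non-randomised contrast. The documents do not show how far it departs from the effect of the briefing.

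As written, SAP 6.2.2 does not trigger the primary pain ANCOVA if 1a fails, about 14–20% of the time under the planned 1a effect, with 14% the closer figure if nearly all 150 complete the 1a questionnaire. The hierarchical procedure itself is sound.

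**What to change.** In SAP 3.3.2 and protocol 11.2:

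- Label 56–65% as the power of a stand-alone, unadjusted test of 1b, with n = 128 after drop-out and n = 150 with none.
- Add the two-step power: about 46–55% under independence across the three sample-size cases, at most 57% or 64%, for the unadjusted analysis. State that the correlation between the tests is unknown and that ANCOVA adjustment would raise the figures.
- State that 0.38 comes from a non-randomised comparison of patients with high and low expectations and is an assumption about the briefing effect.

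In SAP 6.2.2, replace the opening condition with wording such as: the primary 1b ANCOVA is always fitted, and its estimate and 95% confidence interval are always reported; only the confirmatory test and claim depend on rejection of null hypothesis 1a.

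The cost is a less favourable stated power and one more reported estimate. No extra patients are needed, and control of the type I error across 1a and 1b is unchanged.

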## 3.4 Framework and Hypotheses

In a first step, research question 1a will be tested. Only if the high expectation briefing significantly changes the expectations (rejection of null hypothesis 1a), research question 1b concerning the effect on pain intensity will be tested. In both tests, the same significance level of  $\alpha = 0.05$  will be used (see also Section 4.1). This hierarchical order ensures to control for multiple testing.

### 3.4.1 Research Question 1a

Null hypothesis:

Expectation after high efficacy briefing = regular efficacy briefing.

The alternative hypothesis is:

Expectation after high efficacy briefing  $\neq$  regular efficacy briefing.

### 3.4.2 Research Question 1b

Null hypothesis:

Pain intensity at the end of acupuncture treatment after high efficacy briefing = pain intensity after regular briefing.

The alternative hypothesis is:

Pain intensity at the end of acupuncture treatment after high efficacy briefing  $\neq$  pain intensity after regular briefing.

### 3.4.3 Research Question 2

Null hypothesis:

Side effects after intense side effect briefing = side effects after regular side effect briefing.

The alternative hypothesis is:

Side effects after intense side effect briefing  $\neq$  side effects after regular side effect briefing.

## 3.5 Statistical Interim Analyses and Stopping Guidance

There will be no interim analyses.

## 3.6 Timing of Final Analysis

After the information was revealed that the actual treatment in the study were different ways of briefing and not the acupuncture (cf. Study Protocol, Section 3.6, Risk/Benefits, p. 21f., and Section 6.2.2, Blinding Procedures, p. 25), the patients could opt to have their data deleted. Data from each

patient is included in the analysis if there is no withdrawal within 8 weeks after unblinding (which took place on 23 January 2018).

### 3.7 Timing of Outcome Assessment

The last patient visit was on 11 December 2017. The mailing of the follow-up questionnaires will be on 7 May 2018. For further details, see Study Protocol, Section 9, Study Procedures, pp. 30ff.

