#### 6.6.5 Pain Intensity, Follow-Up

For research question 1b, the follow-up measurement of pain (outcome variable `nrs_fu_1`) will be analysed as well, using the same method as described in Section 6.2.2. For the imputation of missing values, the following predictor variables will be used:

- pain intensity measured at follow-up (`nrs_fu_1`)
- effectiveness briefing group (EXPBRIEF)
- side effects briefing group (SIDEBRIEF)
- pain intensity at first visit (`screeningb_1a_4a`)
- pain intensity after acupuncture treatment (`nrs_8_1`)
- baseline optimism (`LOT_BL_optim`)
- baseline pessimism (`LOT_BL_pessim`)
- acupuncture therapist (`acupuncturist`)
- gender (`pers_1_2`)
- age (`age`)
- duration of pain at first visit (`painduration`)
- pain bothersomeness at baseline (`nrs_1a_2`)
- pain bothersomeness at the end of acupuncture treatment (`nrs_8_2`)
- depression (`PROMIS_BL_depression.theta`)
- CARE score (`CARE_1a_red1`)

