### **3.6 Risk/ Benefits**

Risks associated with the briefing intervention:

The experimental manipulation of expectations by the briefing intervention will not be mentioned in advance since the study can only explore this effect without disclosing this study aim to patients. Blinding patients about the use of different briefing interventions is essential to get a valid response. The study objectives will be fully explained to the patients after the end of the study (LPLV), which will be after the last acupuncture session and the last measurement of the study outcomes. Patients will be asked for a full retrospective informed consent. If they consent, data about effectiveness and side effects will be used in the analysis. In case of a refused consent data about effects and side effects will not be used. In this case, only basic information from the screening will be used to describe patients who have withdrawn consent. Such a procedure is covered by the legal situation in Switzerland (Schweizerischer Bundesrat, 2009).

The briefing interventions are developed to make sure that ethically problematic situations are avoided. Patients will not be discouraged or demotivated in the regular briefing condition. This briefing condition is quite similar to patient information before regular treatment. Also the condition with a detailed description of side effects will not differ much from the other empirical investigations on acupuncture. The only difference between the information that will be given in the study and regular patient information in daily practice is the use of booster sessions. This

additional booster is necessary to have a stronger briefing intervention. A less strong intervention might have less effect and would require more patients. In order to minimize effort for a larger number of patients a more intensive briefing intervention is necessary.

Risks associated with acupuncture:

All patients will receive an acupuncture treatment, which is a highly effective treatment for CLBP. The effectiveness of our acupuncture treatment is only slightly lower than for the one for a typical Chinese acupuncture which follows the concept of TCM (Traditional Chinese Medicine) and was superior to standard care in a study. Patients also receive the information that they are allowed to use rescue pain medication and they are allowed to seek additional medical support if needed.

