### **9.3.8 Follow up (Visit 9)**

Six months after the last visit, patients will again be contacted and asked to fill out the follow up questionnaire (P12) including NRS (P7) and PROMIS (P3). They will receive the questionnaire by mail and will be asked to send it back to the study office in the prepaid questionnaire.

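### The SAP's only follow-up mailing date falls 104 days after patients were told the true study aim, yet follow-up is analysed as if blinded and at a uniform six months

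*Combined protocol and SAP*

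**What the plan says.** SAP 3.6 describes what patients were told: "After the information was revealed that the actual treatment in the study were different ways of briefing and not the acupuncture". Patients could then ask for their data to be deleted, and data are kept unless a patient withdrew "within 8 weeks after unblinding (which took place on 23 January 2018". SAP 3.7 adds "The last patient visit was on 11 December 2017" and "The mailing of the follow-up questionnaires will be on 7 May 2018". No other follow-up mailing date is given.

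The protocol set a different order. Section 3.6 says that the objectives will be explained "after the end of the study (LPLV), which will be after the last acupuncture session and the last measurement of the study outcomes", and treats patients' ignorance of the briefing comparison as a precondition for valid answers. Section 9.3.8 (Visit 9) says "Six months after the last visit, patients will again be contacted". Section 9.3.9 (Visit 10) then has the patient informed of the aim. Protocol 5.3 differs: it puts disclosure at the end of treatment.

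SAP 3.1 calls the trial double-blind for patients and statisticians, with no end point to the patient blinding. SAP 4.2 lists missing baseline questionnaires, early stopping of acupuncture and opioid use as departures from plan, but not the order of disclosure and follow-up. Under SAP 6.6.5, follow-up pain "will be analysed as well, using the same method as described in Section 6.2.2", the section for primary question 1b. SAP 6.4.3 repeats that analysis with extra covariates. Appendix A.3 and A.4 add nine models each for follow-up PROMIS scores and bothersomeness.

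**The concern.** The intervention here is what patients were told, and the follow-up outcomes are patients' own ratings. Someone who has learned that the briefing was the experiment may rate pain or health differently from someone who believes acupuncture was under test. That reaction could differ between a patient who received the high expectation briefing and one who received the regular briefing. A follow-up difference could then partly reflect the disclosure, and a missing difference could mean that disclosure cancelled an effect. Neither can be read simply as persistence or fading of the briefing effect.

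Followed as written, the plan would report follow-up contrasts from a trial described as double-blind, at a nominal six months, with nothing to warn the reader. The multiple imputation of follow-up pain has a related weakness. Withdrawal after disclosure and non-response to a later questionnaire may depend on how the patient took the news, and the predictor list in SAP 6.6.5 contains nothing about disclosure.

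**Working it through.** The plan states no figure to reproduce; the check is calendar arithmetic.

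**Inputs.** Last patient visit 11 December 2017 and mailing 7 May 2018 (SAP 3.7). Disclosure 23 January 2018 and the eight-week withdrawal window (SAP 3.6). Follow-up at six months (Protocol 9.3.8). First patient first visit planned for March 2016 and four weeks of treatment (Protocol synopsis). SAP version date 29 May 2018 (SAP 1.2).

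**Intervals.**
- Last visit to disclosure: 43 days.
- Disclosure to mailing: 104 days (104 / 7 = 14.9 weeks).
- Last visit to mailing: 43 + 104 = 147 days; 147 / 30.4375 = 4.8 months.
- Withdrawal window: 23 January + 56 days = 20 March 2018, which is 104 − 56 = 48 days before the mailing.
- Six months after the last visit: 11 June 2018, so the 7 May mailing is 35 days early for that patient.

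**Share of answers given after disclosure.** The SAP does not say whether 7 May was one mailing for everyone, so there are two cases.

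1. *One mailing, the literal reading of SAP 3.7.* Every answer is post-disclosure. The shortest interval since treatment is 4.8 months. If the first patients finished between 1 and 28 April 2016 (assumption), the longest is 24.3 to 25.2 months.
2. *Individual mailings at six months (assumption).* Patients whose last visit fell after 23 July 2017 reached six months after 23 January 2018. From 23 July to 11 December 2017 is 141 days. If last visits were spread evenly from 15 April 2016 (605 days), the share is 141 / 605 = 23%. Starting the spread on 1 April (619 days) or 28 April (592 days) gives 141 / 619 = 22.8% or 141 / 592 = 23.8%. The start date therefore matters little; the even spread matters a great deal and is undocumented.

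Case 2 also fits SAP 3.7 poorly, because an individual six-month mailing for the last patient would fall on 11 June, not 7 May.

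**Handling in the SAP.** SAP 6.6.5, the follow-up part of 6.4.3 and the 9 + 9 = 18 models in A.3 and A.4 contain no restriction, covariate, sensitivity analysis or caveat for disclosure or time since treatment.

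**Date to confirm.** The SAP is dated 22 days after 7 May but puts the mailing in the future tense.

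**The case against.** The strongest reply is that little depends on this. On the SAP's dates, all three primary outcomes were complete 43 days before disclosure, so no confirmatory test, significance level or sample size is touched. Follow-up pain is a secondary outcome, the appendix models are further inquiries, and Protocol 11.3.3 already makes secondary intervals and p-values explorative. This stands, and it limits the severity. It does not remove the point: explorative status concerns error rates, not whether answers were given blind.

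A reader might infer that patients were unblinded to their own arm. The documents do not show that. SAP 3.6 says that they learned what was being compared. Protocol 9.2.3 and 9.3.9 have patients guess their allocation after or at disclosure, and Protocol 6.3 intends no code break. The accurate description is that follow-up answers were given after patients knew the aim.

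A reader might also infer that omitting disclosure and elapsed time biases the briefing comparison. That does not follow. Under a single mailing, disclosure status is constant and cannot be estimated, and a pre-disclosure comparison would have no patients. If answers straddle the date, randomisation in small blocks (SAP 3.2) keeps the arms similar over calendar time, so a covariate for elapsed time is optional. Restricting the main comparison to pre-disclosure answers would discard randomised data and is a debatable choice. The difficulty lies mainly in what the contrast means.

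Finally, the protocol is not uniform. Section 5.3 puts disclosure at the end of treatment, and January 2018 does follow the planned last patient last visit of December 2017 in the synopsis. The 5.3 wording needs reconciling with 3.6, 9.3.8 and 9.3.9. It does not rescue follow-up, since disclosure at the end of treatment would make every follow-up answer post-disclosure.

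**Conclusion.** The point holds for the follow-up outcomes only. The date order is certain on the SAP's text: disclosure precedes the only stated mailing by 104 days, reversing the Visit 9 and Visit 10 order, and that mailing is 4.8 months after the last patient's visit instead of six. The blinding statement, the list of deviations and the analysis sections take no account of either fact.

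The affected share is not established. It is 100% under a single mailing and otherwise an unknown part. The figure of 23% rests on two undocumented assumptions (individual six-month mailings and evenly spread last visits) and should not be quoted as an estimate. The documents do not support extending the criticism to primary outcomes 1a, 1b or 2. This should be fixed before follow-up results are reported, but it does not threaten the trial's main conclusions.

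**What to change.** 1. In SAP 3.1, limit the statement of patient blinding to outcomes collected through session 8.
2. In SAP 4.2, list the reversed order of disclosure and follow-up, and the off-schedule follow-up. Reconcile the protocol passages on when disclosure happens.
3. In SAP 3.7, state whether 7 May 2018 was the only mailing and confirm the date.
4. For each questionnaire, derive disclosure status (before or after 23 January 2018) and time since session 8.
5. If answers straddle 23 January 2018, keep the comparison of all randomised patients in 6.6.5, 6.4.3, A.3 and A.4, add a sensitivity analysis by disclosure status, and include that status in the imputation model for follow-up pain.
6. If all answers came after disclosure, say that follow-up was collected after patients learned the study aim, describe the range of elapsed time, and do not interpret the result as a blinded test of a lasting briefing effect.

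The cost is SAP wording and two derived variables, with no new data collection provided that mailing or completion dates were recorded (assumption; SAP 6.2.3 already uses session dates). The follow-up conclusion becomes less favourable, and any pre-disclosure subset will be smaller and less precise.
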